### Endpoints of the study

Primary endpoint: N1 responder rate / latency of N1 – as the most prominent peak of LUT SEPs.

Secondary endpoints: A) Latencies (P1, P2), amplitudes (P1, N1, P2, P1N1, N1P2), topographies and source localizations of LUT SEPs; B) CPTs; C) latencies, amplitudes, topographies and source localization of tibial, pudendal SSEPs; D) 3-day bladder diary, scores of questionnaires (i.e. ICIQ-FLUTS [30]/ICIQ-MLUTS [31], IPSS [33], IIEF [35] /FSFI [36], Swiss German OAB [34], ICIQ-LUTSqol [37], Qualiveen [32], HADS [38], MoCA [39]).

### Determination of sample size

Based on data from a previous study [25], the sample size was determined using a non-parametric approach [40]. Non-parametric smoothing estimates (kernel smooth) were iteratively compared for subsets of individuals in order to establish the smallest subset (sample size) in which a significant outcome was observed. Determined using cross-validation [41], the smoothing parameter was set to 20. From the smoothed curves, the empirical second derivatives (as an expression of the 'information', i.e. latency, amplitude and dispersion, contained therein) were used, the estimates of which were computed and standardized by the absolute value of their mean. The difference between the two frequencies (0.5Hz and 3Hz) was taken into account, to allow for a standardized vector summary of the curve. Normality was tested using the Kolmogorov-Smirnov method and no evidence against was revealed. A *t*-test based on this standardized vector was subsequently conducted. Power analysis was performed using a bootstrapping technique [42, 43]. For each different sample size combination, the difference between the two frequencies, contained in the standardized vector, was analyzed. The bootstrap simulations were executed at the individual level. All elements of the standardized vector summary were first sub-sampled before results were presented based on the mean p-values for all possible combinations. To ensure robustness of the results, four different criteria – standard deviation, variance, total variance (sum of the absolute values) and *wigglyness* (sum of the absolute values of the second derivatives) – were applied to the standardized vector. The aforementioned procedure was repeated for the different study visits and simulation sites. This resulted in a required sample size of 50 male and 40 female subjects, taking into account potential dropouts.

### Data management and analysis

All EEG data will be filtered and segmented using Brain Vision Analyzer 2 (Version 2.1.0.327, Brain Products, Gilching, Germany). The segments will be averaged and the P1, N1, P2 latencies as well as the P1N1 and N1P2 amplitudes will be determined.

Study data will be collected and managed using the Research Electronic Data Capture Tool (REDCap, Version 6.12.1, Vanderbilt University) electronic data capture tools hosted at Balgrist University Hospital [44]. REDCap is a secure, web-based application designed to support data capture for research studies, providing 1) an intuitive interface for validated data entry; 2) audit trails for tracking data manipulation and export procedures; 3) automated export procedures for seamless data downloads to common statistical packages; and 4) procedures for importing data from external sources.

Primarily, all data will be examined using exploratory data analysis (EDA) methods and described providing mean and standard deviation (or median and range where appropriate). ANOVAs or independent sample t-tests (or Kruskal-Wallis test or Mann-Whitney tests where appropriate) will be performed to compare participant characteristics between groups or to detect gender differences. Linear mixed effects models will be used to compare the two measurement visits. The level of significance will be 5% (alpha = 0.05). Regression techniques will be taken into account, if needed. All the statistical analyses will be performed with the software RStudio (Version 0.98.1083) [45].

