**Methods:**

This study is a prospective, randomized trial conducted at Balgrist University Hospital, Zürich, Switzerland. Ninety healthy subjects (forty females and fifty males) without lower urinary tract symptoms are planned to be included in the study. All subjects will undergo a screening visit (including standardized questionnaires, 3-day bladder diary, urinalysis, medical history taking, vital signs, physical examination, neuro-urological examination) followed by two measurement visits separated by an interval of 3 to 4 weeks. Electrical stimulations (0.5Hz-5Hz, bipolar, square wave, pulse width 1 ms) will be applied using a custom-made transurethral catheter at different locations of the lower urinary tract including bladder dome, trigone, proximal urethra, membranous urethra and distal urethra. Every subject will be randomly stimulated at one specific site of the lower urinary tract. Sensory evoked potentials (SEP) will be recorded using a 64-channel EEG cap. For an SEP segmental work-up we will place additional electrodes on the scalp (Cpz) and above the spine (C2 and L1). Visit two and three will be conducted identically for reliability assessment.

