**Fig. 1 Fig1:**
[figure not shown]
Example of a cortical LUT SEP recorded at Cz with the markers of the P1, N1 and P2 peaks and the corresponding latencies and peak-to-peak amplitudes

In this study we would like to advance the evaluation of viscero-sensory afferent pathways of the LUT and to refine the methodology of LUT SEPs in healthy subjects. We aim to get more knowledge on the impact of different stimulation parameters (e.g. stimulation frequency) on the reliability, shape, latency, amplitude and topographical distribution of SEPs recorded during electrical stimulation of the LUT. In a first step it is our goal to find a frequency that allows a faster acquisition of reliable SEPs than the previously used 0.5 Hz [25, 26] and to obtain normative LUT SEP data for the different localizations in the LUT from different gender groups. In a second step we aim to implement the optimized methodology into clinical practice to use it as an objective marker of pathological LUT conditions and to show distinction of healthy LUT neurophysiology and function.

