## Methods and design

### Study design

This study is a prospective, randomized trial conducted as a single center study at the Spinal Cord Injury Center & Research Lab, Balgrist University Hospital, University of Zürich, Zürich, Switzerland. The study comprises three visits of which the first will be a screening visit followed by two measurement visits separated by an interval of 3–4 weeks (Fig. 2). The site of stimulation will be indicated by random group assignment (in females and males: dome, trigone, proximal urethra, distal urethra; in males additionally: membranous urethra). Consequently, ten females and ten males will be allocated to one localization. In addition, the frequencies used for the stimulation of the LUT and thereafter the SSEP measurements will be randomly applied.

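### The only analysis stated for the two measurement visits compares them, which on its natural reading tests for a systematic shift and does not quantify the test-retest reliability the visits are meant to assess

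*Protocol article*

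**What the plan says.** The Methods part of the abstract gives the reason for repeating the measurement: "Visit two and three will be conducted identically for reliability assessment". The last paragraph of the Background makes reliability part of the research question. The study is to learn how stimulation parameters act "on the reliability, shape, latency, amplitude and topographical distribution of SEPs recorded during electrical stimulation of the LUT", and the first-step goal is "to find a frequency that allows a faster acquisition of reliable SEPs than the previously used 0.5 Hz". The Discussion repeats this aim.

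In Data management and analysis, one sentence covers the analysis of both visits: "Linear mixed effects models will be used to compare the two measurement visits". The next sentence reads: "The level of significance will be 5% (alpha = 0.05". No ICC, within-subject SD, limits of agreement or responder concordance is named. Reliability does not appear under Endpoints of the study. The primary endpoint there is N1 responder rate / N1 latency. Determination of sample size rests on a contrast of 0.5 Hz with 3 Hz and has no reliability target.

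**The concern.** A comparison of visits and an assessment of reliability answer different questions. The comparison asks whether the group as a whole moved between visit two and visit three. Reliability asks whether the same person gives about the same N1 latency, amplitude or responder status twice, relative to the differences between people. Large individual scatter in both directions leaves the group unmoved. A small uniform shift in very repeatable measurements moves it clearly.

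At stake is the evidence for the chosen frequency. The Discussion plans to carry the optimised frequency, and the latency and amplitude cut-offs from this study, into patients with spinal cord injury and multiple sclerosis. Individual cut-offs depend on within-subject error, which a visit comparison does not report.

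**Working it through.** **Plan's own figures.** The article gives no reliability figure to reproduce. The stated total cannot be re-derived either, because it comes from a bootstrap on earlier curves. The allocation does check: five male sites × 10 + four female sites × 10 = 50 + 40 = 90. This agrees with "Consequently, ten females and ten males will be allocated to one localization" (the membranous urethra has males only) and with "This resulted in a required sample size of 50 male and 40 female subjects, taking into account potential dropouts".

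**Inputs.** From the article: n = 90 in total, 10 per sex-by-site cell, 20 per site with both sexes, alpha 0.05. Assumed: two-sided test, normal data, total SD = 1, and every ICC and shift value below.

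**Test of the visit effect.** With complete pairs and a random subject intercept, the visit effect was treated as a paired t-test:

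- SD of the within-person difference = √(2(1 − ICC))
- noncentrality = d·√n / √(2(1 − ICC)), where d is the visit shift in SD units
- chance of p < 0.05 from the noncentral t distribution with n − 1 degrees of freedom

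*No shift (d = 0).* The noncentrality is 0 for every ICC, so the test is significant 5% of the time and non-significant 95% of the time. Simulation at ICC = 0 gave 5.1% significant with n = 90 and 5.2% with n = 10.

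*Shift of 0.1 SD, 90 pairs.* At ICC 0.20 the SD of the difference is √1.6 = 1.265 and the noncentrality is 0.1 × 9.487 / 1.265 = 0.75. At ICC 0.95 they are √0.1 = 0.316 and 0.1 × 9.487 / 0.316 = 3.00.

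| ICC | Chance of a significant visit effect |
|---|---|
| 0.20 | 12% |
| 0.50 | 16% |
| 0.80 | 32% |
| 0.90 | 56% |
| 0.95 | 84% |

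Simulation of the last row also gave 84%. The figure falls to 77% with 75 complete pairs and 67% with 60.

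*Shift of 0.3 SD, 10 pairs (one sex-by-site cell).* 10% at ICC 0.20 and 76% at ICC 0.95.

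**Reliability in the cases most often significant.** Absolute-agreement ICC with a shift d is ICC / (1 + d²/2). For ICC 0.95 and d = 0.1 it is 0.95 / 1.005 = 0.945. For d = 0.3 it is 0.95 / 1.045 = 0.91. Reliability stays high where a significant difference is most likely.

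**What the same model can give.** Two simulated data sets with n = 90 were fitted with a random-intercept mixed model. True ICC 0.30 with no shift gave a visit p of 0.33 and a variance-component ICC of 0.25. True ICC 0.95 with a 0.2 SD shift gave p < 0.001 and an ICC of 0.94. The model recovered reliability both times, while the visit p-value pointed the other way.

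**Precision of an ICC.** For an observed one-way ICC of 0.75 with two visits, F = (1 + 0.75) / (1 − 0.75) = 7. The 95% limits are (F_L − 1)/(F_L + 1) and (F_U − 1)/(F_U + 1). F_L is F divided by the 97.5% point of F(n − 1, n), and F_U is F times the 97.5% point of F(n, n − 1).

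| n | 95% CI |
|---|---|
| 10 | 0.30 to 0.93 |
| 20 | 0.48 to 0.89 |
| 90 | 0.64 to 0.83 |

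**The case against.** The strongest reply concerns the reading. The sentence does not mention means, a fixed visit effect or a visit p-value, and it is not labelled as the reliability analysis. A mixed model with a random subject effect yields between- and within-subject variance, and so an ICC. Which output is reported could be the kind of detail that an article leaves to a fuller document.

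Much of this stands. That the visit effect will be tested is an inference, though the natural one for a comparison placed beside a 5% level. A reader might go further and infer that the planned model cannot measure reliability. That is not supported, because its variance components can. A reader might also infer that an unreliable frequency will pass and a reliable one fail. The article states no pass/fail rule based on the visit p-value, and does not say that the visit comparison selects the frequency.

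The appeal to condensation carries less weight. The article is not silent on the two visits: it names a method, and the use it states for that method does not serve the purpose it gives. That reproducibility was shown earlier does not settle the matter, since the Background gives 0.5 Hz as the frequency used before and the open question concerns faster ones. A reliable SEP could also mean one that is dependably obtained, which the responder rate addresses, but the abstract still ties the repeated visit to reliability.

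The magnitudes are illustrative, as the objection would also say. The 95% is 1 − alpha. The 84% needs all 90 subjects with paired latencies, although 90 already allows for dropouts and N1 latency exists only in responders.

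**Conclusion.** The point holds as a mismatch between a stated purpose and the stated use of a suitable model. On the natural reading, the visit comparison detects a systematic shift and leaves test-retest reliability unquantified. For any fixed non-zero shift, a significant visit difference becomes more likely as reliability improves, so neither a significant nor a non-significant result can stand in for a reliability estimate. The 12% to 84% range rests on a 0.1 SD shift, normal data, a two-sided test and 90 complete pairs; the direction does not depend on those particular values. A linear model also does not suit N1 responder status, which is binary and half of the primary endpoint. No flaw in the design follows: the paired data needed are already being collected.

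**What to change.** In Data management and analysis, replace the sentence on comparing visits with a statement that:

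- reliability is estimated for each stimulation frequency from the mixed model's variance components, as an absolute-agreement ICC with 95% CI and a within-subject SD (or limits of agreement), for N1 latency and amplitudes among subjects with an N1 at both visits;
- reliability of N1 responder status is reported as agreement between visits two and three, by a method for binary data;
- for the frequency comparison, estimates are pooled over site and sex with both as fixed effects, so that differences between sites or sexes do not inflate the ICC;
- site-level values are descriptive, because intervals at n = 10 to 20 are wide;
- the visit effect is kept only as a check for systematic shift, and its non-significance is not read as reliability.

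The cost is analysis wording and slightly more analysis on the same data, with no extra subjects or visits. The drawback is that imprecise site-level estimates become visible.

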## Discussion

This clinical trial will investigate the effect of several stimulation frequencies at different locations of the LUT. Since it was already shown that SEPs could be reproducibly recorded from the LUT [25], we now aim to optimize the settings to achieve a faster acquisition of reliable SEPs, which is important for implementation into clinical diagnostics and to minimize measurement bias through changes that occur over time such as bladder volume.

The assessment of normative values of LUT SEPs in healthy male and female subjects will give us more knowledge on the variability of LUT SEPs, as well as potential factors that may influence the shape and the reliability of the SEPs. Cut-offs for amplitude and latency values can be defined for future investigations in patients with LUT dysfunction. The advancement of neurophysiological assessment methods for the LUT will significantly influence the evaluation of afferent nerve function in the LUT and has the potential to serve as a clinical diagnostic tool complementary to standard urodynamic investigations. After having refined our methodology, we would like to apply LUT SEPs with the optimized stimulation frequency in different patient groups suffering from LUTS, including patients with spinal cord injury and multiple sclerosis. Established cut-off amplitudes and latency values from this study should then be used to relate LUT symptoms and dysfunction in patients with LUT SEP data, thus amending FC findings with an objective evaluation of afferent LUT nerve function in these disorders.

### Trial status

At the time of manuscript submission, first subjects have been recruited, included and investigated.

## Abbreviations

AE: Adverse event
CPT: Current perception threshold
EDA: Exploratory data analysis
EEG: Electroencephalography / electroencephalogram
FC: Filling cystometry
GCP: Good clinical practice
LUTS: Lower urinary tract symptoms
OAB: Overactive bladder
SAE: Severe adverse event
SDV: Strong desire to void
SEP: Sensory evoked potential
UTI: Urinary tract infection
